## Abstract

**Background:**

Cancer patients have to undergo a difficult medical therapy and are also confronted with various psychological, social and economic problems. Support is available from many providers, but patients often gain no access to it. Accordingly, there is a need for a single point of contact that can provide advice, information and assistance. In the state of Saarland, Germany, a supportive new consulting and information path (PIKKO) for all types of cancer is currently evaluated by the German Cancer Society, the Cancer Society of the Saarland, three statutory health insurances and the Jena University Hospital. PIKKO is designed to improve quality of life, self-efficacy, health literacy and patient satisfaction and to reduce psychological distress, related health care costs and the days of inability to work. This methodical work presents the process and analysis planning of this evaluation.

**Methods:**

The study population includes all cancer types, both new and existing diseases. PIKKO (with patient navigator, oncological knowledge database, specialized oncological counseling) is evaluated within a controlled, non-randomized, comparative, multicenter, longitudinal design. In addition to patient surveys, data from statutory health insurances and utilization data from the web database are collected, and interviews with patient navigators and doctors are carried out. Patients are assigned to a control (usual care) or an intervention group (u. c. + PIKKO). Primary outcome is the health related quality of life (SF-12) six months after baseline. Secondary outcomes are self-efficacy (GSE), psychological distress such as depression (PHQ-9) or anxiety (GAD-7), health literacy (HLS-EU-Q47) and patient satisfaction in health care (Qualiskope-A). Furthermore, the time course of direct costs of medical care (e.g. work disability days) and usage data of the intervention modules are analyzed. Among other statistical procedures, we use t-tests, univariate tests and growth curve models.

**Discussion:**

If PIKKO proves to be effective, recommendations can be made to health organizations, which should lead to the concept being rolled out throughout Germany and included into oncological guidelines. We expect PIKKO to be a useful addition to usual cancer care, helping to improve the quality of life of cancer patients and reduce healthcare costs.

**Trial registration:**

This study was retrospectively registered in the German Clinical Trial Register under DRKS00016703 (21.02.2019, the reason for the delay was the prioritization of the study management in the first year to establish the new approach into practice). https://www.drks.de/drks_web/navigate.do?navigationId=trial.HTML&TRIAL_ID=DRKS00016703

## Background

### Background and rationale

The treatment of cancer became more successful in the past decades. Simultaneously cancer incidence is increasing due to an aging and growing population [1]. More and more patients have to be treated and the individual survival is higher than ever before [2].

Cancer means a major change in the patient’s life and is usually associated with psychosocial distress [3]. In many cases the financial situations of cancer patients is getting worse, because patients are not or only partially able to work [4]. More than half of those affected do not feel sufficiently informed about the legal benefits to which they are entitled [4]. In addition to this psychosocial and financial burden, patients need high quality, evidence-based and helpful health information [5]. The satisfaction with respective information is related with the quality of life of patients [6]. On the other hand, regularly available health information is not suitable for laymen, especially in terms of readability and understandability [7]. This becomes even more important as patients want to actively participate in decision making concerning their therapy [8, 9], which is only possible if all relevant information on the individual medicinal situation is easy accessible and understandable. Handling complex medical information and making decisions out of them requires health competence [10] and professional advice. But there are barriers to a balanced advice from physicians, not at least because of information asymmetry and consequential communicative deficiencies between physician and patient [11–13]. In Germany, cancer patients have an average of more than 40 doctor contacts per year [14]. Many patients are treated by different specialists whereby treatment is oriented towards different national guidelines [15]. Less than 50% of patients are completely satisfied with treatment, communication, information, participation, collaboration between specialists or psychosocial aspects [16]. This calls for an adequate source of information for patients. A direct and permanent contact person for the patients and their relatives seems worthwhile.

One promising solution for a better and low threshold integration of patient needs is a patient navigation program. In 1990, [name] initiated the first patient navigation program in the USA. This early program (and other followers after the Patient Navigator and Chronic Disease Prevention Act passed by the US Congress in 2005) tried to eliminate the barriers to timely care across all segments of the healthcare continuum. A real person, a patient navigator (PN), is the most important part of these programs [17]. Usually this person is a specialized trained nurse or medical assistant.

In many cases PN are specialized to a single type of cancer e.g. breast cancer or lung cancer [18]. These concepts were accompanied by studies and showed positive effects of PN [18–20]. Fillion reports a better emotional quality of life and satisfaction in the PN exposed cohort [21]. A higher quality of life (especially physical and social functioning) in an experimental group (nurse navigation) was assessed by Lee [22]. A tendency to lower distress scores was seen regarding patients that used an oncological nurse navigator [23, 24]. A PN can decrease anxiety and increase satisfaction, e.g. after abnormal mammogram [25] or with newly diagnosed primary breast cancer [24].

To cover the complex needs of patients regarding navigation in German health care and access to evidence-based and understandable information across all cancer types a comprehensive intervention program was initiated in 2017 in Germany by the German Cancer Society, the Cancer Society of the Saarland, the Jena University Hospital and three statutory health insurance companies (IKK Südwest, Knappschaft and Techniker Krankenkasse). The program is called “Patient information, communication and competence empowerment in oncology (PIKKO)”. PIKKO supplements the usual care with a new consulting and information path.

PN have also been tested in other chronic diseases such as diabetes, AIDS, cardiovascular disease, chronic kidney disease or dementia [26]. For such cases, PIKKO could also serve as a model of feasibility in Germany.

The evaluation aims to measure the effect of PIKKO on a patient level (better quality of life, less psychological stress, better self-efficacy, better health competence, more satisfaction with the practitioners), as well as on the level of health care costs which should provide information on the implementation of the care concept and the transfer to other diseases. This paper describes the evaluation concept.

## Methods / design

### Objectives

PIKKO focuses on communicative aspects and informative needs of cancer patients and consists of four modules. The patients receive (1) the advice of a trained PN and (2) an access to a new database with evidence based information about cancer. Furthermore a fast access to a specialized oncological counseling is guaranteed (3). Finally, a ring folder is provided to patients to cope the paper flood during their illness (4). Within the project the new consulting and information path (treatment as usual plus PIKKO) is integrated to usual care (Fig. 1).

**Fig. 1 Fig1:**
[figure not shown]
The PIKKO concept and the central patient navigator

This concept is intended to become a well-established program in the German health care system for all cancer patients. But before that the PIKKO concept must be evaluated. The evaluation focuses on patients and their health-related quality of life (HRQoL) particularly the mental component. We expect that patients who underwent PIKKO report a higher HRQoL, less mental impairment such as depression and anxiety, better self-management and higher health literacy than patients of the control group. Furthermore, we expect lower direct health care costs (days of inability to work, sick-pay, expenses of health benefits).

### Trial design

The design of the evaluation study consists of four components: patient surveys, data provided by statutory health insurance companies, interviews with service providers as well as the usage data of the oncological knowledge database. The non-randomized, controlled, comparative, multicenter, longitudinal design included three groups: experimental group (treatment as usual plus PIKKO), first control group (treatment as usual; active recruited; questionnaire and health care data) and second control group (treatment as usual; random selection, only anonymous health care data). A non-randomized design with two recruitment periods, starting with the (first) control group, was chosen due to the following reasons: 1) randomization on a test person level was not possible for ethical reasons and for reasons of the statutory basis of the German health care system. 2) It is also not reasonable from a CRM (Customer Relationship Management) perspective to withhold an existing service from needy persons on the part of the statutory health insurances. 3) In a medical facility (practice, clinic), intervention and control cannot take place simultaneously to the extent required by this study (control patients could still contact PN). 4) Cluster randomization was not feasible for a project of this size and kind due to the medical infrastructure in the small state of Saarland. Accordingly, the periods were set one after the other and later the participants of the control group have the option to switch to the intervention group. Secondly, to establish the new intervention with all the descripted modules the German Cancer Society, the Cancer Society of the Saarland and the health care insurance companies needed time, nearly one year. However, no time should be lost in terms of data collection, so it was used for the patient survey of the control group. The date of recruitment determines the group assignment. The control group is included in the first project year (while the new intervention is under development) and the intervention group is recruited in the second year (when the new consulting and information path is available). A third group is a random selected sample of patients who are not part of the two other groups. Only health care data are collected for these persons. This second control group allows examining the representativeness of the sample respectively the selection process and the comparisons of treatment courses.

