### Recruitment

To recruit physicians to participate in PIKKO, the consortium leader (IKK Südwest) organized internal (invitations to the IKK Südwest) and participated in external (health-related congresses and similar) information events. They are addressed to all physicians of different specialization that are involved in care of cancer patients: oncologists, gynecologists, urologists, general practitioners, internists, and other. The participating hospitals, clinics, and medical practice must sign a study contract to participate in the supply concept PIKKO and to recruit patients. The enrollment is conducted by physicians or trained medical staff e.g. a nurse.

For the recruitment of PN, mailings were made to all participating hospitals, clinics and practices. Up to ten persons can be trained with a two weeks course by the German Cancer Society. Target group are people who already work in the field of cancer-related health care such as oncological nurses, social workers or other non-medical staff of an oncological outpatient clinic or oncological department of a hospital.

The patients are recruited in various ways. Firstly, they can be addressed directly while attending a medical consultation (outpatient or inpatient) as long as they show the inclusion criteria. The enrollment is carried out directly. Secondly, a landing page at the internet serves as a contact point to patients who hear about PIKKO via mass media such as newspaper articles and radio program or on various events about cancer [27]. The potential participant is using a contact form and receives a phone call by his/her health insurance company. Eligibility criteria are checked and a local enrollment is arranged. Thirdly, health insurance companies can recommend their members to attend the study. The enrollment is carried out by post. And fourthly patients can actively ask their physician, statutory health insurance, the German Cancer Society, the Cancer Society of the Saarland or the evaluator. In this case the potential participant will be led to a local enrollment person.

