### Participant timeline

The enrollments of the two allocation groups take place in two consecutive enrollment periods. Every period lasts one year starting with the control group.

The patients express interest to participate in the supply concept to the enrollment person who reviews the inclusion and exclusion criteria. Furthermore, the enrollment person informs and educates the patient and hands over the oncological ring folder. After successful enrollment a standardized form is sent to the statutory health insurance company and to the evaluator. This informs the evaluator about the patient assignment and the agreement to establish contact (e.g. by telephone).

From this point in timeline there are small differences between the two groups in collecting the baseline data.

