### Data management

#### Data organization

Contact and process information are saved in a database which is programmed with Microsoft Access especially for this evaluation (names; address; telephone number; allocation; contact events, outgoing or incoming of questionnaires; date of enrollment; date of dispatch; date of fill out; enrollment person; PN; withdrawal; data entry). The database keeps track the patients’ timeline and allows intervening if the time interval between the patient questionnaires becomes too large (algorithm and alerts). In addition, the database enables the cooperation partners to be kept up to date in terms of recruitment and study process (reports and summaries). Access is multiple times secured for privacy reasons.

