### Statistical methods

Characteristics of control and intervention groups (e.g. age, sex, education, family situation, partner situation) will be analyzed with descriptive statistics. Since no randomization is made for ethical and research practical reasons, univariate tests are used to determine which of the above mentioned characteristics differ between the two groups. Ideally there are no significant differences between the two groups. In the case of significant differences we will compute propensity scores using the corresponding pre-treatment variables. Then, we will apply in the subsequent analyses propensity scores as stabilized regression weights to reduce bias caused by different group characteristics.

The main hypothesis of an intervention effect on psychological and physical health, self-efficacy, health care costs etc. will be proofed by the comparison of averages of intervention and control group (resp. t-tests). To estimate the corresponding regression adjusted group means we will use growth curve models. Furthermore, we will conduct subgroup analyses to identify conditional treatment effects.

For dropout analysis we will conduct a logistic regression with dropout as criterion and group assignment and baseline variables as predictors applying the regression weight mentioned above. For the time-to-event analysis we will conduct a Cox regression.

The level of significance will be α = 0.05. To validate our analyses, we will conduct the analyses with imputed missing data and without imputation.

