### Limitations

In general, less burdened patients, patients with a stronger self-motivation, patients with higher self-efficacy or patients with more social support could preferably participate, leading to a selection bias. Related with this bias can be an overestimation of treatment effects when the treatment is especially effective for less burdened patients. Also an underestimation of the mortality or patient’s withdrawal is possible. To examine the selection bias, we included a second control group which is a random sample of eligible patients based on health insurance company data. We expect that the selection bias is small so that the generalizability of study results should be high.

The voluntary and selective participation of hospitals (respectively individual departments), clinics and practices could lead to a selective clientele of patient e.g. disproportionately many breast cancer patients. However, this could also make the study more comparable to the many studies that have been pre-determined for certain groups, e.g. specialized in breast cancer patients [18].

Due to ethical and other reasons (described in the section “Trial design”) the design is not randomized. To compensate for this limitation, we will use propensity scores for analyses [58, 59].

Since we will collect questionnaires from seriously ill and elderly patients, we might expect incomplete questionnaires. Missing items and missing complete questionnaires should be compensated by imputation of missing data [44, 45].

Each participant agrees with the use of his data from the statutory health insurance companies. These data are collected from all included patients without their direct participation. However, to collect questionnaire data, we rely on the direct support of the patients. The number of data sets can therefore vary between data from the questionnaires and from the statutory health insurance companies.

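### Enrolment date fixes the group, so volunteers under the two offers may differ, and the planned propensity adjustment is switched on only by significant baseline differences

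*Protocol article*

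**What the plan says.** On allocation, Trial design states: "The date of recruitment determines the group assignment". It adds "The control group is included in the first project year (while the new intervention is under development"). Intervention patients were to be enrolled a year later, once the service was running. Trial status puts the changeover at 31 October 2018.

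On how patients arrive, Participant timeline says: "The patients express interest to participate in the supply concept to the enrollment person who reviews the inclusion and exclusion criteria". Recruitment lists four routes: approach in a consultation, a landing page fed by media coverage, recommendation by the insurer, and the patient's own request ("And fourthly patients can actively ask their physician, statutory health insurance, the German Cancer Society, the Cancer Society of the Saarland or the evaluator").

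On adjustment, Statistical methods begins: "Characteristics of control and intervention groups (e.g. age, sex, education, family situation, partner situation) will be analyzed with descriptive statistics". It then uses univariate tests to find which of these differ. If some differ significantly, it builds propensity scores from those variables and applies them as stabilised weights. Limitations names propensity scores as the compensation for not randomising.

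On selection, Limitations describes who is likely to take part in general, assigns the second control group to examine this, and concludes: "We expect that the selection bias is small so that the generalizability of study results should be high".

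**The concern.** With a date rule, the group is known to whoever enrols before the patient is approached. That patients knew it too is an inference, though a strong one: they came forward for a care concept whose navigator, database and counselling did not exist in the first period. Someone who volunteers for a folder and questionnaires need not resemble someone who volunteers for a navigator. The mix of the four routes may also shift once there is help to offer. Trial status adds a further insurer that joined during the intervention period only.

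Selection of this kind is not only a question of generalisability. If it differs between the periods, it enters the six-month SF-12 contrast directly. The direction cannot be predicted: more distressed joiners in the second period would hide an effect, and more motivated ones would create one.

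The written safeguard depends on a significance test. In a non-randomised comparison, that test answers a question about sample size, not about confounding. A moderate imbalance that misses p < 0.05 is left out of the score, and if nothing is significant there is no weighting at all.

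**Working it through.** **Inputs.** From Sample size calculation: d = 0.25, two-sided α = 0.05, power 0.90, 338 analysed and 507 recruited per group, dropout one third. The size of any imbalance or bias is assumed.

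**1. The plan's own figure.** n = 2(1.960 + 1.282)² / 0.25² = 336.2, so 337 per group by the normal approximation. The t-test gives 337.2, so 338, with power 0.901. Dropout: 338 / (1 − 1/3) = 507, total 1014. The plan's figures reproduce.

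**2. How often the trigger fires.** For one continuous characteristic at baseline the standard error of the difference is √(2/507) = 0.063 SD. For an imbalance of 0.10 SD, 0.10/0.063 = 1.59, and the chance of exceeding 1.96 is about 36%.

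| Imbalance (SD) | Detected, 507 per group | Detected, 338 per group |
|---|---|---|
| 0.05 | 12.5% | 9.9% |
| 0.10 | 35.6% | 25.5% |
| 0.15 | 66.5% | 49.5% |
| 0.20 | 88.9% | 73.8% |

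**3. What a residual difference does to the primary test.** At 338 per group the standard error is √(2/338) = 0.077 SD. Let b be the difference in the SF-12 mental score, in SD, left by selection after adjustment.

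| b (SD) | Rejection rate with no true effect | Power at d = 0.25 if b works against it |
|---|---|---|
| 0 | 5% | 90.1% |
| 0.05 | 9.9% | 73.8% |
| 0.10 | 25.5% | 49.5% |
| 0.15 | 49.5% | 25.5% |

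One way to reach such values: if a share s of the intervention group joined only because of the offer and differs by g SD, then b = s × g. Examples are 20% × 0.25 = 0.05 and 20% × 0.5 = 0.10.

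**4. The two tables must not be run together.** A missed imbalance in a covariate passes to the outcome only in proportion to its standardised slope r, so b = imbalance × r. A missed 0.10 SD imbalance with r = 0.5 (assumed) gives b = 0.05. Several missed imbalances can add up or cancel. An unmeasured motive never meets the trigger at all.

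**5. Can the second control group show it?** Trial design gives that group health care data only, and Data collection methods says the insurer data cannot be matched to questionnaires. It therefore cannot show a difference in SF-12.

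**The case against.** A reader might infer that the plan ignores selection between the groups. It does not. Statistical methods ties the univariate comparisons to the lack of randomisation, and Limitations offers propensity scores as the remedy. What can be criticised is the rule, not its absence.

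A reader might also infer that adjustment is confined to demographics. The list is introduced as examples, so it is not closed. Table 1 collects SF-12, PHQ-9, GAD-7, GSE, social support, cancer status and chronic disease at T0 in both groups, and the growth curve models may absorb part of a baseline difference. More distressed joiners would therefore be partly visible. This stands, and it is why the fix is cheap. It does not rescue a rule that uses a variable only when its test is significant.

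The absence of enroller and route from the stated analysis is not a finding. The article is condensed, and such detail may sit in a document not shown.

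Other points stand in part. Table 2 gives diagnoses, costs of psychological therapy and days of inability to work by allocation group, so each period's volunteers could be compared with the random sample on those; this could reveal differential selection but not correct SF-12. Controls may switch later, which weakens the incentive to wait. Eligibility names initial diagnosis, relapse or transition to palliative care, so freedom to time one's entry should not be overstated.

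**Conclusion.** The point holds in a limited form. Allocation was open and predictable, so selection can differ between the groups. The written rule makes adjustment depend on significance and misses a 0.10 SD imbalance in a given characteristic about 64% of the time at 507 per group. Limitations frames selection as a matter of who participates at all, which understates the threat to the primary contrast.

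The size of any actual bias is unknown. The figures for 0.05 and 0.10 SD (false-positive rate about 10% and 25%, power about 74% and 49%) show sensitivity and are not estimates. They assume 338 analysed per group, an unweighted t-test and a bias that remains after adjustment. The documents do not support a claim that the result is biased, or in which direction. No weighting will remove differences in help-seeking or motivation that were not measured.

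**What to change.** **(a) Statistical methods.** Compute the propensity score whatever the univariate tests show. Always include new versus existing disease and cancer status at T0, baseline SF-12, PHQ-9, GAD-7, GSE, social support and chronic disease. Add recruitment route where it can be recovered from the enrolment form; it is not among the fields listed in Data organization. Keep the univariate tests as description only.

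**(b) Supportive sensitivity analysis.** Repeat the six-month contrast within enrolment person or facility, pooling small ones, among those who recruited in both periods. The tracking database already holds what is needed ("date of enrollment; date of dispatch; date of fill out; enrollment person; PN; withdrawal; data entry"). With about 80 physicians and 338 analysed per group, there are on average 338/80 = 4.2 patients per physician per group, so pooling is unavoidable. State that this removes fixed differences between enrollers but not a change in who volunteers to the same enroller. It should not decide whether an effect is claimed.

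**(c) Limitations.** Say that enrolment was not concealed, that selection can therefore differ between the groups and bias the contrast, and that weighting cannot remove unmeasured help-seeking or motivation.

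**Cost.** Revised wording, one further model and some work to recover route. Weights become slightly more variable and the sensitivity analysis is less precise. The main analysis keeps every patient and the sequential design is unchanged.
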